## Abstract

**Background:**

Despite smoking cessation can largely improve cancer prognosis and quality of life, many patients continued smoking after the diagnosis of cancer. This study aims to test the effectiveness of a smoking cessation intervention using risk communication approach to help cancer patients quit smoking, and to improve their health related quality of life.

**Methods:**

A cluster randomized controlled trial will be employed. Cancer patients who continued smoking after the diagnosis of cancer and have medical follow-up at the out-patient clinics of the five acute hospitals in Hong Kong will be invited to participate. Subjects in the experimental group will receive (1) health warnings of smoking based on a special designed leaflet; and (2) a patient-centred counseling from nurse counselors with emphasis on risk perceptions of smoking to cancer prognosis. Additionally, they will receive two more telephone counseling at 1-week and 1-month. Control group receive standard care and a generic self-help smoking cessation booklet. Outcomes measure include (a) self-reported and the biochemically validated quit rate, (b) patient’s smoking reduction by at least 50 % compared to baseline, (c) quit attempt(s), (d) change in the intention to quit, (e) change in risk perceptions of smoking, and (f) change in health related quality of life.

**Discussion:**

This study will make an important contribution to evidence-based practice by testing the effectiveness of a tailored smoking cessation intervention for cancer patients. The results will support the development of clinical practice guidelines to promote smoking cessation in cancer patients to improve their prognosis and quality of life.

**Trial registration:**

ClinicalTrials.gov NCT01685723. Registered 9 November 2012.

## Background

Smoking is the most significant preventable cause of cancer in the world [1]. Research indicates that current smokers have a twofold to threefold increased risk of cancer, and about 90 % of lung cancers are attributed to smoking [2, 3]. Apart from lung cancer, cigarette smoking can cause many different types of cancer including cancer of the oropharynx, larynx, oesophagus, trachea, bronchus, acute myeloid leukaemia, stomach, liver, pancreas, kidney, ureter, and bladder, and colorectal [2].

Recent advances in medical technology have dramatically improved the survival rate for most types of cancer. However, cancer patients who continue to smoke are at greater risk for second primary, cancer recurrence, and all causes of mortality [4]. Furthermore, cigarette smoking can not only reduce the effectiveness of medical treatments for cancer including radio- and chemo-therapies [5, 6], but also increase the risk of therapy-related side-effects [7]. Conversely, there is strong evidence that quitting smoking after being diagnosed with cancer could reduce the risk of disease advancement [8], minimize adverse treatment-related effects, improve prognosis, and enhance the quality of life [9]. Given the beneficial effects of cigarette smoking cessation and the hazardous effects of continued smoking on cancer patients’ physical and psychological health, it is of paramount importance for healthcare professionals to help this vulnerable group to quit smoking [10].

Medical attention at out-patient clinics of smokers who had been diagnosed with cancer can be developed as an excellent “teachable model” as it provides an invaluable opportunity for them to initiate smoking cessation to improve their health. It also presented healthcare professionals with a golden opportunity to advise smokers to quit while they are waiting for medical consultation or follow-up. Nevertheless, cigarette smoking is addictive and quitting is very difficult, with a high rate of relapse, particularly among those chronic patients with high nicotine dependency [11, 12]. Previous studies showed that 47 % smokers with lung cancer in USA and about one third of cancer patients in western countries continued to smoke after receiving a cancer diagnosis [4, 13–15].

In a recent qualitative study [16] investigating the risk perceptions, and the behaviour, attitudes, and experiences of Chinese current smokers and ex-smokers who have been diagnosed with cancer, the results reveal that many of the informants had inadequate knowledge of the association between smoking and cancer. Besides, many informants who continued smoking were unaware of the beneficial effects of quitting, including ameliorating adverse effects of treatment and improving prognosis and quality of life. Furthermore, many informants had misconceptions that a moderate amount, such as half a pack of cigarettes per day, was not detrimental to their physical health. Some even believed that quitting would harm their physical well-being as their bodies had become desensitized to the chemicals in tobacco after long-term smoking. Additionally, some informants were worried about losing the “psychological benefits” of smoking once they quit and thus perceived barriers to quit outweighed the perceived benefits. The findings of this study [16] address an important yet under-researched area, as very few smoking cessation programs targeting cancer patients, and only very few healthcare professionals help this vulnerable group to quit smoking [17]. There is an imperative need for healthcare professionals to design special interventions that use strong warning to clearly communicate the risk of continued smoking to this group as a strategy to enhance their motivation to quit. The findings of the study [16] provide a guide for developing an effective intervention protocol that will demystify the misconceptions about smoking among these vulnerable individuals and increase their perception of the risks of continued smoking and benefits of quitting.

### Current study

The present study aims to test the effectiveness of a specially designed smoking cessation intervention using a risk communication approach for cancer patients who are smokers, to (i) achieve a higher quit rate, (ii) improve their smoking behaviour, (iii) motivate their intention to quit smoking, (iv) improve their risk perceptions of continued smoking, and (v) improve the quality of life.

### Conceptual framework

The theoretical framework is shown in Fig. 1. The framework is constructed with reference to the nicotine addiction context in smoking [18], and a modified Theory of Planned Behaviour (TPB) to guide the development of the smoking cessation intervention [19]. We assume smokers who have cancers will quit smoking if they have positive attitudes, subjective norms and perceived control on quitting, while the antecedents are mediated by intention. In addition, we will use a risk communication approach in the Self-Regulation Model of Illness [20] to influence patients’ attitudes toward quitting (behavioural beliefs) and their normative beliefs. We will apply part of the Transtheoretical Model (TTM) to guide the risk communication (in form of the pros and cons of behavioural change) and increase the self-efficacy of participants [21]. The concept of risk perceptions have been found to be a cue to promote healthy behaviour among patients.

**Fig. 1 Fig1:**
[figure not shown]
Theoretical framework – a modified Theory of Planned Behavior (TPB) model

## Methods/Design

The study design is shown in Fig. 2. It is a cluster randomized controlled trial to test the effectiveness of a smoking cessation intervention using risk communication approach to help cancer patients quit smoking. The settings will be the oncology out-patient clinics of the five acute hospitals in Hong Kong.

**Fig. 2 Fig2:**
[figure not shown]
Study protocol (CONSORT diagram)

### Study sample and recruitment

Cancer patients fulfilling the following inclusion and exclusion criteria will be invited to participate in the study. The inclusion criteria are: (1) smoked weekly in the past 6 months, (2) diagnosed with cancer that are related to smoking [2], such as cancer of the oropharynx, larynx, lung, oesophagus, trachea, bronchus, acute myeloid leukaemia, stomach, liver, pancreas, kidney, ureter, and bladder, and colorectal, (3) diagnosed with cancer for at least 6 months (such that their conditions and treatments would be stable), (4) patients in all stages I, II, III, or IV, (5) aged 18 or above, and (6) can communicate in Cantonese. The exclusion criteria are: (1) those with unstable medical conditions as advised by the doctor in charge, (2) poor cognitive state, (3) having mental illness, and (4) those participating in other smoking cessation program. The oncologists and oncology nurses will assess and inform us the stability and suitability of the cancer patient to participate. The patients would be at different phases/ stages but they will also be eligible, if confirmed by the oncologists/ oncology nurses.

### Procedure

Approval for the study has been obtained from five hospital ethics committees (Kowloon West Cluster Research Committee; Hong Kong East Cluster Ethics Committee; Kowloon Central/Kowloon East Research Ethics Committee; Hong Kong West Cluster Ethics Committee; and New Territories West Cluster Clinical & Research Ethics Committee). To ensure the rights of all participants will be protected, the research carried out will be in compliance with the Helsinki Declaration (http://www.wma.net/en/30publications/10policies/b3/index.html). Research assistants will approach patients in the oncology out-patient clinic and ask them whether they are smokers or not. The eligible subjects will then invite to participate in this study after they are told the purpose of the study. They will be given the option of participating or refusing involvement in the study and will be told that their participation is voluntary without prejudice. Written consent will then obtain from all participants.

To evaluate the effectiveness of a smoking cessation intervention using risk communication approach, a total of 560 eligible Chinese cancer patients were recruited from five out-patient clinics in Hong Kong. After completing the baseline questionnaire, subjects will receive proposed intervention according to their group assignment. Four consecutive (3-, 6-, 9- and 12-month) follow ups will be conducted by trained interviewers (blinded to the group assignment) with all subjects via telephone. We will assess hospital readmission and other clinical outcomes from the participants’ medical records accordingly. Patients who have successfully quit smoking at 6-month will be invited to come back to the out-patient clinic and have biochemical validation tests (saliva cotinine test and exhaled CO test). We will offer HKD300 (USD38.5) per client to cover their travel expenses and time cost. From our previous experience, such an incentive is necessary to secure a sufficiently high response rate.

#### Training and quality assurance of the nurse counsellors and research assistants

All the research nurses are qualified smoking cessation counsellors, and they will be provided with specific training workshop by the principal and co-investigators prior to the commencement of the study. They will be equipped with the necessary knowledge and skills to deliver both the smoking cessation counselling using the motivational interviewing techniques and stages of change model. Regular case conference, quality checks through audio-taping, and audit procedures will be conducted to ensure and maintain the quality and uniformity of the counselling interventions. The research assistants will be trained by the principal and co-investigators to screen eligible case, conduct baseline and follow-up surveys and procedures of biochemical validations (saliva cotinine test and exhale CO test). Briefing sessions will also be provided to oncologists and oncology nurses in using the special designed leaflets.

Since the same batch of oncologists and oncology nurses working in the setting would contact cancer patients in both the intervention and control group, a quality assurance mechanism will be used to prevent the contamination of intervention and control group: (1) a clear instruction and reminder will be given to the participating doctors and nurses before the start of the RCT study, and we will explain the principle of RCT and reinforce them the different treatments for the experimental and control groups; (2) a specific risk communication leaflet will be attached in front of the patients’ medical records in the intervention sessions, and doctors and nurses will fill up a checklist to make sure if they have delivered the intervention at the end of each consultation; (3) patients in the experimental group will be invited to complete a satisfaction survey during telephone follow-up to see if they have received the risk communication messages from physicians and nurses during baseline intervention; and (4) doctors and nurses will be reminded that they need not deliver the intervention during the “control” clinic sessions and only usual care will be given.

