### Randomisation

Randomization will be done with each session in an out-patient clinic as a cluster unit. Currently there are 10 sessions per week per study site. Before the study, we will randomly draw the sessions by computer generated random sequence (block randomization with each hospital as a block unit), so that 5 sessions will be treated as intervention group and another 5 sessions will be treated as control group per week. Participants who consent to participate in the study will be assigned to either intervention or control group depending on the out-patient clinic session that they are seeking consultation. By using this experimental design, we can ensure similar proportion of smoking cancer patients will fall into the intervention and control group in each out-patient clinic, and each out-patient clinic will have a similar proportion of cancer patients into the intervention/ control group. We expect the intervention and control group would have similar socio-demographic profile, smoking history, and clinical history and we shall check for any differences, and if any, we shall adjust for them in the analyses. In using the cluster randomization design with a session being a cluster unit, the patients who are randomized into the experimental and control groups would have less chance to meet each other in the out-patient clinic and discuss the contents of the smoking cessation interventions.

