### Intervention

#### Control group

Subjects in the control group will receive usual care provided at the site, a generic self-help smoking cessation booklet published by the Hong Kong Council on Smoking and Health, a brief face-to-face counselling at baseline plus telephone follow ups by nurses to show support and care on their disease condition.

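### Interviewer blinding is not secured: it fails if the survey for the experimental arm only is part of the outcome calls, or if recruiting staff telephone their own patients

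*Protocol article*

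**What the plan says.** The Procedure section states that four consecutive "follow ups will be conducted by trained interviewers (blinded to the group assignment) with all subjects via telephone".

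The section on training and quality assurance describes two arrangements that bear on this.

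- As one of its measures against contamination, "patients in the experimental group will be invited to complete a satisfaction survey during telephone follow-up". The stated purpose is "to see if they have received the risk communication messages from physicians and nurses during baseline intervention". Control patients have no counterpart.
- Research assistants are to be trained "to screen eligible case, conduct baseline and follow-up surveys and procedures of biochemical validations".

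Other sections show what research assistants can see in clinic. Under Procedure, "Research assistants will approach patients in the oncology out-patient clinic". Under Randomisation, participants are "assigned to either intervention or control group depending on the out-patient clinic session that they are seeking consultation". In intervention sessions the "leaflet will be attached in front of the patients"' medical records (training and quality assurance section).

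The primary outcome is the 7-day point prevalence quit rate at 6 months, by self-report (Primary and secondary outcomes).

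**The concern.** A survey given to one arm only, about receiving that arm's treatment, identifies the arm. An interviewer who has to give it knows the arm before dialling, or learns it during the call. An assistant who recruited a patient in a given session can also know the arm, because the session determines it.

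Patients know what counselling they had, and the primary outcome is what they say on the telephone. Blinding the person who asks and records is the main protection the protocol states against uneven probing and recording between arms. If that protection is lost, no analysis can restore it.

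**Working it through.** **Step 1. The survey.** Procedure: the outcome interviewers are blinded. Training and quality assurance: the survey is for experimental patients only, takes place during telephone follow-up, and asks about the experimental treatment. The text does not say who gives it, at which call, or whether the smoking questions come first.

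- *Within the 3- to 12-month outcome calls.* The interviewer learns the arm. If the survey precedes the smoking questions, that call's outcome is affected. If it follows them, that answer is safe, but any later call by the same interviewer is not.
- *Within the 1-week or 1-month nurse calls.* The nurse counsellors already know the arm, so no outcome interviewer is unblinded, provided the answers are not passed on.

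The first is the more natural reading. The outcome calls are the ones described as scheduled telephone follow-ups that collect survey data, whereas the Experimental group section describes the nurse contacts as telephone intervention and counselling.

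**Step 2. The staff.** One role covers screening, baseline surveys, follow-up surveys and biochemical validation. Recruitment takes place in sessions whose arm is fixed before the study. The article neither separates recruiters from callers nor says that the session is withheld from callers. This route does not depend on where the survey falls.

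**Step 3. Biochemical validation as a safeguard.** It is a secondary outcome, is offered at 6 months only to patients who report having quit (Procedure), and is done by the same staff role. It can show some false claims of quitting, but it does not protect the primary comparison.

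**Step 4. What a bias could do (illustration).** The stated sample size is taken as input, so I reproduced it first (Power calculation: 29% vs 18%, 5% level, 80% power, 15% attrition, intra-class correlation 0.002).

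- n = [1.96·√(2·0.235·0.765) + 0.842·√(0.29·0.71 + 0.18·0.82)]² / 0.11² = 233 per group after rounding up (two-sided, pooled variance, no continuity correction). Stated: 233.
- 233 / 0.85 = 274.1. Stated: 274.
- 274 × [1 + (13.7 − 1) × 0.002] = 281.0 with 20 sessions per arm (274/20 = 13.7 patients each). Stated: 280.

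Now let true quitting be 18% in both arms (the plan's control rate), with n = 280 per arm, and let recorded quitting in the experimental arm be 18% + d. With p̄ the mean of the two recorded rates:

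- SE₀ = √[2p̄(1−p̄)/n]; SE₁ = √[(p₁(1−p₁) + p₂(1−p₂))/n]
- P(reject) = Φ[(d − 1.96·SE₀)/SE₁] + Φ[(−d − 1.96·SE₀)/SE₁]

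For d = 0.02: SE₀ = √(2·0.19·0.81/280) = 0.03316, SE₁ = √[(0.16 + 0.1476)/280] = 0.03315, and P = 0.0874 + 0.0052 = 0.093.

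| Assumed over-recording d | Patients (280·d) | Two-sided rejection |
|---|---|---|
| 0 | 0 | 5.0% |
| 2 points | 5.6 | 9.3% |
| 3 points | 8.4 | 14.6% |
| 4 points | 11.2 | 21.9% |
| 5 points | 14.0 | 31.0% |

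Nearly all the excess favours the intervention: at 5 points, 31.01% in its favour against 0.03% in the other direction.

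**The case against.** The strongest reply is that the article never places the survey in an outcome call. It uses similar words for nurse contacts: control patients get "telephone follow ups by nurses to show support and care on their disease condition", and Potential limitations or barriers uses the same term just after describing the counselling calls. A check on what happened at the baseline intervention also fits an early nurse call. Likewise, a list of what research assistants are trained to do does not say that the person who recruits a patient later telephones that patient. Different assistants could do each job, and both statements would then hold.

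This stands as far as it goes. A reader might infer that blinding is already broken, or cannot be achieved. The documents do not support that, because each route needs a fact the article does not state.

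It can also be said that a condensed article leaves rostering and question order to the full protocol. That would answer a complaint about missing detail. Here the article itself claims blinding and then describes procedures that, read naturally, conflict with the claim.

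Two further points are fair. Patients may give the expected answer whoever telephones, and blinding the interviewer does not remove that. Control patients also receive face-to-face counselling and nurse calls, which narrows the difference in attention. Neither point makes uneven recording by an interviewer who knows the arm harmless.

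Finally, the bias sizes in the illustration are assumed. The same table would follow from any bias of that size, so it is not evidence that this bias occurs.

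**Conclusion.** The concern holds in conditional form. If the experimental-arm survey is part of the outcome calls, or if recruiting staff telephone their own patients, the stated blinding fails for a self-reported primary outcome. On other readings the blinding is possible but not secured by what is written. Validation at 6 months is only a partial safeguard.

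The size is unknown. The range of about 9% to 31% rejection, against a nominal 5%, rests on an assumed over-recording of 2 to 5 points, 18% true quitting in both arms, 280 analysed per arm, a normal approximation and no cluster effect. No figure stated in the article changes. This is a cheap improvement, not proof that the trial's primary result would be biased.

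**What to change.** Reconcile the Procedure section with the training and quality assurance section as follows.

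1. Take the arm-specific survey out of the blinded outcome calls. Either the nurse counsellors, who already know the arm, collect it at the existing 1-month call, or someone other than the interviewer collects it after the outcome has been recorded. If follow-up calls remain after that point, keep the survey answers from the interviewers.
2. Roster the existing research assistants so that none telephones patients from a site where he or she recruited.
3. Leave session and arm off the call sheets.

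The cost is rescheduling one short questionnaire and some rostering effort, with no extra staff or patients. The change is of use for the primary outcome only if it is in place before the 6-month calls.

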#### Quality and data security control

This study will follow the protocol of quality assurance developed by a previous project [22]. The principal and co-investigators, project coordinator and nurse counsellors will set up orientation meetings with oncologists, nurse managers and frontier nurses to explain the protocol, the flow of logistics and examine the physical facilities available in the hospital. The principal and co-investigators will answer any queries raised by oncologists and nurses immediately at any time point. The project coordinator will be present during the first week to monitor the subject recruitment and data collection process. All blank and completed instruments will be sealed in separate opaque envelopes, which will be kept in a locker with keys provided by hospitals, while the project coordinator will collect the filled instruments weekly by hand. All collected instruments will be saved in a locker with keys in the institution of the principal investigator. The project coordinator and other research assistants of this project will be responsible to input the data into SPSS, with the dataset encrypted in an assigned personal computer.

